### Exclusion criteria

Exclusion criteria include:

• Unable to read or write English; or

• Aged less than 18 years; or

• Known* limited life expectancy (under one year)

** The caveat of 'known' is used, as it may not be possible to determine limited life expectancy of relatives*.

We have not made special arrangements for non-English speaking participants for two reasons:

• Paget's disease is extremely rare in non-Caucasians and therefore we anticipate that English will be the first language of virtually all, eligible individuals within the UK.

• The instruments used in this study (in particular the BIPQ and TPB) are sophisticated and sensitive tools for measuring an individual's perceptions of treatment and illness. Translating these measures into alternative languages necessitates re-validation of these instruments, which would require considerable investment of time and financial resources that are not available for this study.

Individuals with limited life expectancy are excluded from Stage 2 of the study as the process of completing a questionnaire may be cognitively and emotionally taxing for them.

A lower age limit has been imposed (minimum age of 18 years). Clinical studies suggest that people with *SQSTM1 *mutations develop Paget's disease from approximately 45 years of age onwards [7]. Clinical intuition would suggest that starting a programme of preventive treatment at age 40 years would therefore be appropriate. The clinical evidence to support this, however, is still lacking. In addition, it is likely that a psychologically 'acceptable' age for beginning preventive treatment will differ from that indicated by existing evidence. As such, we propose to include all adult relatives of probands to determine the effect of age of the acceptability of genetic testing, and preventive treatment.

### Consent Process

Although implied consent will be assumed if a subject completes and returns a questionnaire, we have additionally incorporated a brief consent form into the questionnaire to ensure that the following points are clearly understood:

• The general purpose of the study and questionnaire are understood;

• That the subject can withdraw from the study at any time and if they specifically request it, their data will be destroyed;

• The data is collected and securely stored by the Despatch Office in Edinburgh;

• We are not able to offer a genetic test or preventive treatment for Paget's disease as part of this study;

• That a summary of the results can be sent to them if they indicate agreement.

It is explicitly stated in the consent forms and questionnaires that participants can withdraw from the study at any time by contacting the study office and, if requested, their data will be destroyed.

The consent form incorporated into the questionnaires will also contain a tick box for participants to indicate whether they wish contact about future research projects concerning Paget's disease.

### Measures

A questionnaire will be sent to probands. This questionnaire will include:

• Details of disease presentation in the proband;

• An overview of the family structure;

• Details of relatives to contact.

A questionnaire will be sent to first and second-degree relatives of probands. This questionnaire will include specific measures of:

• All variables hypothesised to affect the likelihood of uptake of a programme of genetic testing and preventive treatment (potential explanatory variables; see section 6.1); and

• Dependent variables measuring the acceptability or intention to take up an offer of a programme of genetic testing and preventive treatment.

In addition, each section of the questionnaire will have a section of open questions.

### Potential explanatory variables

#### Illness and Emotional Representations

Illness and Emotional Representation will be assessed using the *Brief Illness Perception Questionnaire (BIPQ) *[33]) adapted for Paget's disease of bone. This is a very widely used predictive measure. Adaptations for specific conditions are part of the standard use of the questionnaire and [name] will provide critical feedback relating to the adapted measure before use. Appropriateness of items will also be tested for Discriminant Content Validity [44].

### Representations of Testing and Treatment Behaviours

Based on Stage 1 interviews, a questionnaire will be designed to assess beliefs about the behaviours involved in accepting a programme of genetic testing and preventive treatment, using TPB constructs and methods. The constructs are:

• *attitudes *to accepting a programme of genetic testing and preventive treatment;

• *subjective norm *refers to beliefs that important others would wish one to accept or not;

• *perceived behavioural control *refers to beliefs that a programme of genetic testing and treatment will be offered which they are able to accept; and

These constructs will be assessed using standard TPB methods [40] and based on beliefs (behavioural, normative and control) elicited in Stage 1. All measures will contain at least 3 items so that reliability can be assessed and will be subjected to psychometric analyses.

### Respondent characteristics

Age, gender, marital and employment status; relationship with affected person(s), number of affected relatives; self-assessed health as measured by SF-12 and self-assessed health on standard 4-point rating scale (excellent, good, fair, poor).

### Presentation of the disease in affected relative(s)

The following data will be collected from the proband: age at onset, previous fracture, previous bone surgery and the number of bones affected by Paget's disease. In addition, the SF-36 will give standardised measures of impairment, activity limitations, and participation restriction, based on previous work on the relationship between this measure and the ICF health components [45].

### Dependent variable: Acceptability of a programme of genetic testing and preventive treatment

Acceptability will be assessed through: intention to accept a test if offered and intention to accept preventive treatment if recommended by doctors. In addition, relatives' perceptions of the feasibility of taking preventive treatment will be measured through perceived behavioural control of particular forms of treatment. Intention and perceived behavioural control will be assessed using standard TPB methods [40].

Measures will be developed to assess *probability *of acceptance, using both numerical and verbal-rating scales and guidance from work on presenting probabilistic risk data. Using the TPB it is possible to measure intention and to assess the probability of engaging in the described behaviour. Information from Stage 1 interviews will be used for content, phrasing and context, and piloted in interviews until satisfactory. Participants will be specifically asked whether they would take up a programme of genetic testing and preventive treatment if it were to become available. In addition, we would specifically investigate the acceptability of the following options: preventive treatment options (tablet or infusion); and location of clinical intervention for preventive treatment (primary or secondary care; regional specialist centres or local.

### Data collection

Potential participants will be assigned a unique study number. This information will be held on a password-protected database/spreadsheet at the University of Edinburgh.

Questionnaires will be pre-labelled with these study numbers and posted to the corresponding potential participants. Questionnaires will be identifiable by the unique study number only.

Probands and relatives will be asked to complete and return the questionnaire in a reply-paid envelope. Help in completing the questionnaire will be available if required. If the patient is known to have difficulty writing (for example due to severe arthritis), is deaf or blind, special arrangements will be made for completion of the questionnaires.

[name], the Chief Investigator, and a data manager based at the Queen's Medical Research Institute, Edinburgh, will coordinate the administration of questionnaires and data management. Stage 2 will therefore be administrated from this site, and will be Sponsored by the University of Edinburgh.

Data will be returned by participants to the Edinburgh Office. There it will be entered onto an electronic database (password protected and stored on secure University server). An experienced data clerk will enter the data from questionnaires into this database. Anonymous data from this database will be transferred to the GaP study office at the University of Aberdeen for statistical analysis.

### Quality Assurance

Full verification checks will be undertaken at the time of data capture. A random 10% sample of data will be double entered to check accuracy. Extensive range and consistency checks will further enhance the quality of the data.

### Analysis

Stage 2 data analyses will involve psychometric assessment of developed and adapted measures. The main analyses will be carried out by a statistician in collaboration with [name], an expert in the psychometrics and analysis of theoretically based measures and analyses. and will involve multiple and logistic regression; this will be approached systematically, starting with analyses for each theoretical approach and then for each group of variables to identify significant predictors which will then be brought into an overall predictive equation.

Answers to open ended questions will be analysed to clarify content. The analysis of open questions will not involve a full qualitative analysis of all responses, but instead will be analysed as required to aid interpretation of quantitative results. Members of the research team will carry out this analysis. Detailed qualitative analysis may be carried out in the future and will be subject to separate funding and ethical approval.

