### Scientific value of this study

This project takes advantage of recent advances in knowledge about the molecular-genetic basis of PDB, with advances in therapeutics to address an important clinical question that is of relevance to patients with Paget's disease and their families. The project provides added value in that modern techniques and models in behavioural science will be applied to a specific issue in the treatment of Paget's disease, while at the same time investigating more general theories of human behaviour. Using the Common Sense Model of Self-Regulation, we will investigate how genetic information and preventive opportunities affect self-regulation via illness representations and, using the Theory of Planned Behaviour, how the behaviour of uptake of the offer of genetic testing and treatment is predicted by the constructs found to predict behaviour in other settings. Thus, the findings will be relevant to these theories. They will also contribute to ongoing work to integrate these two models in understanding cognitions and behaviour related to illness threats [38].

In addition, the knowledge gained from this investigation would be relevant to other musculoskeletal diseases such as osteoporosis, which also have a strong genetic component, and which can be prevented by bisphosphonates and hormone replacement therapy. With completion of the human genome project, and advances in human molecular genetics, it is probable that DNA testing with single genetic markers or combinations of markers will be offered for a wide range of other chronic diseases for which effective treatments are available. The results of the present research project will also be of direct relevance to the development of programmes of genetic testing and preventive intervention for these conditions.

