### Sample Size

Given that most of these individuals have already engaged in research, we anticipate a high participation rate and estimate that 70% of probands will have living blood relatives and will be happy to contact their relatives. Based upon the experience of a recent study of familial hypercholestorolaemia [41] it is anticipated that an average of 2 relatives per participating proband will participate. The recommended minimum sample is calculated as 50 + 8 m, where m is the number of predictor variables [42]. This study has a total number of 26 predictor variables and the minimum sample size required is 258 relatives.

We anticipate that there will be a clustering effect of responses within families. The size of clustering effect is determined by the intra cluster correlation, and the sample size needs to be inflated to reflect this correlation [43]. We have no prior evidence of the possible size of this clustering effect, so assuming that the study has an average cluster size of 2 relatives per proband and that the correlation was 1 (the worst case scenario), the inflation factor would be 2. We therefore intend to recruit a minimum of 516 relatives to account for this effect. To achieve this it will be necessary to approach a minimum of 369 probands (accounting for 70% participation rate). We intend to approach a random sample of 200 probands with a known family history of Paget's disease, and 200 without.

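### Screening predictors for significance by theory and by group, then refitting the survivors on the same data, makes the final overall equation look better than it is

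*Protocol article*

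**What the plan says.** The Analysis section states that the main analyses "will involve multiple and logistic regression". Of the order of work it says that "this will be approached systematically, starting with analyses for each theoretical approach", followed by analyses "for each group of variables to identify significant predictors which will then be brought into an overall predictive equation". The article names no significance level for the screen, does not list the groups, and mentions no full model or correction for selection.

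The Sample Size section gives the rule: "The recommended minimum sample is calculated as 50 + 8 m, where m is the number of predictor variables". It applies the rule to the whole candidate list: "This study has a total number of 26 predictor variables and the minimum sample size required is 258 relatives". For family clustering it assumes an "average cluster size of 2 relatives per proband and that the correlation was 1 (the worst case scenario"), so that "the inflation factor would be 2" and the target becomes 516 relatives.

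Under Scientific value of this study, the authors say of the findings: "They will also contribute to ongoing work to integrate these two models in understanding cognitions and behaviour related to illness threats".

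**The concern.** The overall equation contains only variables that have already passed a significance test on the same respondents. Its printed statistics are calculated as if those variables had been chosen in advance. Four outputs are affected:

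- the overall test, which no longer has its nominal error rate;
- R-squared, which is inflated by the choice of the best-looking variables;
- the coefficients of the survivors, which are biased away from zero because estimates that fell low by chance were dropped;
- the survivors' p-values, which ignore the selection.

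The study exists to say which factors relate to acceptability, so the combined equation is likely to be the result most quoted. The Dependent variable section lists more than one outcome (intention to accept a test, intention to accept treatment), and the problem recurs for each. This is a rule that the article states, not a detail left to a fuller analysis plan.

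**Working it through.** **The plan's own figures.** With m = 26, 50 + 8 × 26 = 258. The design effect with 2 relatives per proband and a correlation of 1 is 1 + (2 − 1) × 1 = 2, so 258 × 2 = 516. Probands to approach: 516 / 2 / 0.70 = 368.6, rounded up to 369. All three match the Sample Size section. By the plan's rule, the target already covers one model with all 26 predictors.

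**Assumptions that are not in the article.** Two-sided 5% screen; five blocks (8/4/6/5/3 predictors, or 7/3/7/7/2 in a second set of runs); continuous outcome; independent observations; correlation between predictors in the same block of 0 or 0.3. Two sample sizes were used. One is 258, which is the effective size if the within-family correlation is 1. The other is 516, which is the effective size if it is 0.

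**Chance that something passes when nothing is real.** For 26 independent tests, 1 − 0.95^26 = 73.6%, with 26 × 0.05 = 1.3 predictors expected to pass.

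**Simulation with no true effects** (2,000 runs per row, blocks of 8/4/6/5/3). Each run fits ordinary least squares within each block, keeps p < 0.05, refits the survivors together, and also fits the fixed 26-predictor model.

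| n | Within-block correlation | Overall F p < 0.05, screened | Overall F p < 0.05, fixed 26 | Mean R-squared if anything selected | At least one false-positive predictor: screened / fixed 26 |
|---|---|---|---|---|---|
| 258 | 0 | 70.2% | 4.8% | 0.037 | 69.3% / 70.3% |
| 258 | 0.3 | 55.6% | 5.0% | 0.034 | 54.6% / 69.2% |
| 516 | 0 | 70.9% | 5.3% | 0.019 | 70.2% / 72.4% |
| 516 | 0.3 | 58.1% | 5.1% | 0.017 | 57.1% / 72.8% |

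Null predictors that passed the screen still had p < 0.05 in the final equation in 66% to 88% of cases. With blocks of 7/3/7/7/2 and no correlation, the screened overall F-test was significant in about 70% of runs at both sample sizes.

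**Simulation with true standardised effects of 0.12.** With three such effects and uncorrelated predictors, the true R-squared is 3 × 0.12² / (1 + 3 × 0.12²) = 0.0432 / 1.0432 = 0.041.

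- n = 258: the mean retained estimate is about 0.17, and 0.17 / 0.12 = 1.42. A run with five true effects gave 0.165, and 0.165 / 0.12 = 1.375. The range is about 37% to 42% too large.
- n = 516: 0.136 / 0.12 = 1.13 and 0.137 / 0.12 = 1.14. Across runs the range is about 12% to 14% too large.
- Adjusted R-squared after screening: 0.055 (n = 258) and 0.049 (n = 516). The full model gives 0.042 and 0.041.
- The full model with every coefficient reported averages 0.12 at both sizes.

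**Logistic models.** The article gives no outcome proportion. If the less frequent response is between 20% and 50% (an assumption), 516 relatives give 103 to 258 events, and 103 / 26 = 4.0 to 258 / 26 = 9.9 events per predictor. At an effective size of 258 these halve to about 2.0 to 5.0.

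**The case against.** Several points on the other side stand.

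- A reader might infer that screening fills the answer with extra chance findings. The table does not support that: at least one false-positive predictor appears in 55% to 70% of screened runs and in 69% to 73% of full-model runs. That is ordinary multiplicity, and fitting the full model does not remove it.
- Inflated effects come from reading only significant results. With five true effects of 0.12 at n = 258, the significant coefficients of the full model averaged 0.178, against 0.169 after screening. The full model cures this only if every coefficient is reported and read whatever its p-value.
- A reader might infer that the rule defeats the aim of comparing or integrating the two theories. The article does not support that. Analyses by theory come first, and nothing says that constructs are deleted from them. Fitted whole, with content fixed beforehand, they are unaffected, and the article claims only a contribution to work on integration.
- A reader might also see a contradiction between 26 predictors in the sample size and a reduced final equation. The article never says that all 26 enter one model, and counting all candidates is compatible with later reduction. The sample size shows only that reduction is not forced by numbers under the plan's rule.
- The larger inflation belongs to the worst-case effective size, and the screening level and blocks are assumed.
- The study informs feasibility and a later trial and states no confirmatory hypothesis.

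What none of this answers is the overall test and R-squared of the screened equation. The test's error rate is as high at n = 516 as at n = 258.

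**Conclusion.** The point holds for the final overall equation. Read as if it had been specified in advance, its overall test, R-squared, coefficients and p-values are too optimistic. With no true effects the overall test is significant in about 56% to 71% of runs against a nominal 5%; the lower end applies with a within-block correlation of 0.3. Mean R-squared when anything is selected is about 0.035 at n = 258 and 0.018 at n = 516. True effects of 0.12 come out about 37% to 42% too large at n = 258 and about 12% to 14% too large at n = 516.

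These sizes rest on the assumed 5% screen, five blocks, continuous outcome and independent observations. R-squared and coefficient bias shrink as n grows; the failure of the overall test does not. To call the results simply invalid would go too far: the fault lies in reading the final equation at face value, and does not extend to the by-theory models.

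**What to change.** For the continuous intention outcomes, replace the significance screen in the Analysis section with the following:

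- enter complete blocks of predictors in a pre-specified order;
- keep all predictors in the final model whatever their p-values;
- report every coefficient with its interval;
- give the change in R-squared for each block with a joint test that allows for family clustering.

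If a shorter equation is wanted, label it exploratory. Report its R-squared corrected for optimism by resampling whole families, with the selection repeated in each resample.

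For the logistic models, choose the predictors or blocks in advance without using p-values, or use a penalised fit. The 50 + 8m rule does not assure enough events for 26 predictors there.

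The cost is some rewording, slightly more analysis work, a longer final equation and wider intervals. Under the plan's own rule no more relatives are needed, because 258, inflated to 516, already allows for 26 predictors.

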### End of Study procedures

During the consent process for the study we will ascertain whether participants would like to be sent a report of the study results.

For those participants indicating that they would like study results, a short report will be prepared and circulated at the end of the study.

Questionnaires will be stored in locked filing cabinets until the study is complete, and will then be anonymised and archived for 20 years in accordance with Medical Research Council guidelines. The Chief Investigator, [name], will act as the Custodian of the data.

### Confidentiality

The Chief Investigator Office, based in the Queen's Medical Research Institute, Edinburgh, is responsible for the confidentiality of all study records. Potential participants will be assigned a unique study number. This information will be held on a password-protected database/spreadsheet at Edinburgh University. Questionnaires will be pre-labelled with these study numbers and posted to the corresponding potential participants. Questionnaires will be identifiable by the unique study number only. In accordance with Good Clinical Practice, and Institution codes of conduct, all data will be password protected against unauthorised access and stored in accordance with the Data Protection Act 1998. All stored data will be anonymised.

### Reporting and Dissemination

A summary of the results of the study will be prepared and distributed, not only to the appropriate funding body, but also to all participants (if they so wish). Results will be published in peer-reviewed journals to make the results available to both researchers on bone disease and researchers on health-related behaviours.

